#### Cardiometabolic health

The cardiometabolic variables that will be analyzed are glucose, insulin, triglyceride, total cholesterol, and glycated hemoglobin. Blood samples will be collected from the antecubital vein in vacuum tubes after 12 hours of fasting following the recommendations of the Brazilian Society of Clinical Pathology/Laboratory Medicine, at two different moments (baseline and postintervention). Fasting glucose will be measured using the reference enzyme with Hexokinase. To determine fasting insulin, the chemiluminescence method will be used. The total cholesterol and triglycerides will be analyzed by the enzymatic colorimetric method, and glycated hemoglobin will be determined using high-performance liquid chromatography. The homeostasis model assessment for insulin resistance (HOMA-IR) will be used to determine insulin sensitivity, and will be calculated using the following formula: [(glucose* 0,0556)*insulin]/22,5 [59].

#### Mental health

The anxiety, depression, and stress symptoms of the participants will be assessed using the Depression and Anxiety Stress Scale-short form (DASS 21) [60, 61]. This scale comprises 21 questions using a 4-point Likert-type scale (0 = not at all, 3 = almost always), covering three dimensions of mental health status(S3 File). The total score of each dimension will be multiplied by two and scores ranged from 0 to 42.

The well-being will be measured by two domains of the KIDSCREEN-27 questionnaire (S3 File), physical well-being consists of 5 items, and psychological with 7-item. For each item, participants respond using a scale with scores from one to five points [62].

Sleep quality and quantity will be collected by Pittsburgh Sleep Quality Index (PSQI) [63], which is validated for Brazilian adolescents [64]. The PSQI is a self-reported questionnaire(S3 File) that asks respondents to report their sleep quality and signs of sleep disturbance for 1 month before completing the questionnaire. The PSQI includes 19 questions, categorized into seven groups (sleep quality, sleep latency, sleep duration, habitual sleep efficiency, sleep disturbance, use of sleeping medications, and daytime dysfunction). Each constituent question produces a score on a 4-point Likert-type scale (from 0 to 3) and the total score is made up of scores from each of the seven subgroups of questions, giving a cumulated score between 0 and 21.

#### Anthropometric assessments

Body mass will be measured to the nearest 0.1 kg in light clothing without shoes using a portable digital scale (Welmy®, Santa Bárbara do Oeste, São Paulo, Brazil) and height will be recorded using a portable stadiometer (Welmy®, Santa Bárbara do Oeste, São Paulo, Brazil). Both weight and height will be measured twice to reduce the risk of measurement error. A third measurement will occur if there is a difference of >0.1 kg for body mass and >0.3 cm for height between the first and second measurements. Body mass index (BMI) will be calculated using the standard equation (body mass [kg]/height [m]2) and BMI-z scores will be determined using the ‘LMS’ method according to World Health Organization data [65]. Waist circumference will be measured twice at the midpoint between the last rib and the iliac crest using steel tape (Sanny®, São Bernardo do Campo, São Paulo, Brazil). A third measurement will occur if there is there be a difference of >0.3 cm for WC.

#### Healthy lifestyle

Screen time will be estimated by the following question: “during an ordinary weekday, how many hours do you spend watching TV, using a computer, smartphones or playing video games?” (except Saturday, Sunday, and holidays) [66]. Eating behaviors will be assessed by questions about the frequent consumption of ultra-processed/embedded food, sugary foods, snacks, and sugar drinks. Also it will be asked about breakfast by the following question:”Considering a normal week, how many days do you have breakfast?” [67]

### Hypothesized mediators

#### Resistance training self-efficacy

Self-efficacy will be assessed by a four-item scale(S3 File) developed specifically for use with adolescents [68], and the participants will respond about their confidence to engage in resistance training using a 5-points Likert (1 = strongly disagree to 5 = strongly agree).

#### Basic psychological needs satisfaction

The ‘Adolescent Psychological Need Support in Exercise Questionnaire’ will be used to evaluate friends´ and teachers’ support for exercise [69] (S3 File). The evaluation of this instrument requires satisfaction during exercise across the three-item: autonomy support, relatedness support, and, competence support. Participants reported their satisfaction using a 7-point Likert scale ranging from *1 ‘strongly disagree’ to 7 ‘strongly agree’*.

#### Autonomous motivation

The ’Behavioural Regulations in Exercise Questionnaire’ [70] (S3 File) will be used to assess autonomous motivation for physical activity using 2-subscales: identified and intrinsic regulations. Adolescents respond on a five-point scale ranging *from 0 ‘not true for me’ to 4 ‘very true for me’*.

### Control variables

#### Somatic maturation

Biological maturation will be estimated through the evaluation of somatic maturation by determining the distance in years of the individual from the baseline peak height velocity (PHV) using sex-specific mathematical models [71]. This method estimates maturity-offset (in years) from height and chronological age using Eq 1 for boys:

$$\text{Maturity}\;\text{offset}\;\text{for}\;\text{boys}\;\left(\text{years}\right)=-7.999994+\left(0.0036124\times \left(\text{age}\times \text{height}\right)\right)$$
(1)

And using the Eq 2 for girls:

$$\text{Maturity}\;\text{offset}\;\text{for}\;\text{girls}\;\left(\text{years}\right)=-7.709133+\left(0.0042232\times \left(\text{age}\times \text{height}\right)\right)$$
(2)

#### Lifestyle questionnaire

Information on alcohol drinks and tobacco smoking(S3 File) among adolescents will be obtained by two questions: “Do you smoke?” and “Do you alcohol beverage?” in a dichotomous manner (yes or no), through indication of the use during the previous 30 days.

### Process evaluation

Feasibility will be assessed based on the following: 1) consent rate (how many participants offered the program agreed to be involved); 2) retention rate (retention rate at 24-weeks follow-p); 3) attendance (student participation in the structured PA), 4) students´ satisfaction with the program (“I enjoyed participating in the sessions on 5-point Likert scale: 5 = strongly agree to 1 = strongly disagree) (S4 File), 5) engagement (student engagement with the pedometer self-monitoring and adherence to goals setting) and 6) practical session fidelity (three observations per teacher) using the SAAFE observation checklist [48] (S4 File).

### Safety considerations

All measurements, evaluations, and interventions in the context of the present study will be performed in a safe environment, however, if any adverse event occurs, the research team will call the Mobile Emergency Care Service. In addition, adolescents’ vital signs (blood pressure, heart, and respiratory rate) will be continuously monitored during measurements and intervention (if need). All adverse events will be evaluated, recorded, and discussed in the final paper.

### Statistical analyses

#### Analysis plan

Linear mixed models will be used to analyze the primary and secondary outcomes using IBM SPSS Statistics for Windows (version 20.0; 2010 SPSS Inc, IBM Company, Armonk, NY 2010 SPSS Inc., IBM Company, Armonk, NY), with significance set at p< 0.05. All analyses will subscribe to the intention-to-treat principle, whereby all participants will be included in the analysis in the group to which they were randomized. The models will be used to assess the effect of treatment, time and the group-by-time interaction, using random effects to account for the clustered nature of the data. Time and treatment will be included as fixed factors, with school class will be included as a random effect. According previous studies, school-level clustering is negligible after accounting for clustering at the class level [72]. However, if requerid, we will test this assumption and additionally adjust our analyses for school-level clustering. Mixed models are consistent with the intention-to-treat principle, assuming that data are missing at random. The analyses of the primary endpoint (ie, 24 weeks endpoint) will be performed using a repeated measures analysis of covariance applied using mixed linear models. Change from baseline to the postintervention of primary and secondary outcomes will be applied as the dependent variable, treatment (intervention or control), time (baseline and 24 weeks), and the group-by-time interaction will be included as independent variables. To examine the maintenance of the effect of the physical activity program on primary and secondary outcomes, comparable repeated measures approach will be used between group (intervention or control), time (baseline, 24 weeks and 48 weeks), and group-by-time interaction. Effect sizes between groups will be calculated using Cohen’s *d* (the adjusted difference between the control and intervention groups over time divided by the pooled standard deviation of change) and interpreted as follows: *d* = 0.2 (small), *d* = 0.5 (medium), and *d* = 0.8 (large). Potential moderators will be explored using linear mixed models with interaction terms for the following: sex (male, female), socioeconomic status (low, medium, high), and initial BMI status (healthy weight vs overweight/obese). Subgroup analyses will be only conducted if significant interaction effects P≤0.10. Sensitivity analyses will be performed (eg, multiple imputation and complete-case analysis). If the intervention effect estimate differs differs significantly from that obtained when these values are included, both results will be reported in the paper. For completeness in assessing the effect of missingness, we will also conduct one per-protocol analyses (ie, at the student levels). Therefore, our student-level per-protocol analysis, we will include only those students who participated at least 80% of sessions offered across the intervention period (up until our primary end point). Hypothesized mediators (Fig 2) of physical activity behavior change will be examined using structural equation modelling to assess the underlying causal pathways of the intervention.

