### Sample size calculation

The sample size estimation was conducted using G*Power (version 3.1) and based on detecting changes in the primary outcome of PA. Based on previous research, we anticipate the effect size for PA of d = 0.25 (an adjusted for the baseline of 5 min MVPA per day and assuming a standard deviation of MVPA of 17.8 minutes with a correlation of 0.59 between baseline and follow-up) [42]. We adjusted for clustering at the class level using a correction factor of [1 + (m—1) x ICC], where m represents the number of participants per class and ICC refers to the intraclass correlation coefficient for PA, assuming an average class size of 29 participating students, three classes per school and an ICC for PA of 0.034 [43]. Allowing for an expected dropout of 20% at the study endpoint, the required sample size to achieve 85% power with alpha levels set at 0.05 in 174 students (87 in the intervention group and 87 in the control group).

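### The 24-week model is specified in two incompatible ways; where baseline is kept as a level of time, a class random intercept cancels from the group-by-time test and class clustering is covered only if class effects are constant over time

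*Protocol article*

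**What the plan says.** Under Blinding and randomisation, schools are the randomised unit. Under Sample size calculation, the article states "We adjusted for clustering at the class level using a correction factor of" one plus (class size minus one) times the ICC, "assuming an average class size of 29 participating students, three classes per school and an ICC for PA of 0.034". Sizing therefore treats class clustering as something that inflates the variance of the activity effect.

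Under Analysis plan, random effects are meant to deal with clustering, and the terms are named: "Time and treatment will be included as fixed factors, with school class will be included as a random effect". A school-level adjustment is conditional on need. No class-by-time term and no student term is mentioned.

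The 24-week analysis is described as an analysis of covariance for repeated measures, fitted by mixed models. Its dependent variable is the change from baseline to post-intervention. The same sentence lists treatment, time with two levels (baseline and 24 weeks) and their interaction as independent variables. For maintenance, a "comparable repeated measures approach will be used between group (intervention or control), time (baseline, 24 weeks and 48 weeks), and group-by-time interaction".

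**The concern.** There are two linked problems.

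First, the 24-week description combines two models. If the outcome is change from baseline, each student has one value at 24 weeks, and there is no baseline row from which to estimate time or group-by-time. If time has the levels baseline and 24 weeks, the outcome has to be the value at each visit. An analyst must drop one half of the sentence to fit anything.

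Second, the choice decides whether clustering is handled. With one change value per student, a class random intercept is the class-level difference in change, which is what needs to enter the standard error. With baseline as a level of time, the same intercept is shared by all visits and adds nothing to the standard error of group-by-time. What inflates that standard error is classes moving apart between visits. This is plausible here, because PE teachers deliver the sessions within their own lessons. A school intercept added under the conditional clause would cancel in the same way.

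At stake are the error rate and the width of the confidence intervals for the primary outcome, and for the other outcomes analysed this way. The maintenance analysis is the clearest case, because its text has the repeated-measures form.

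**Working it through.** **Inputs from Sample size calculation:** m = 29 per class, ICC = 0.034, SD = 17.8 min, baseline to follow-up correlation r = 0.59, total 174.

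**Assumptions:** six classes (174/29 = 6), two-sided 5%, clustering at class level only, complete data. The class autocorrelation *a* (the correlation of a class's effect between two visits) is not in the article, so it is varied from 0 to 1.

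**1. The plan's own figures.** The design effect is 1 + (29 − 1) × 0.034 = 1.952. The total of 174 could not be reproduced. A difference of 5 min with SD 17.8 × √(1 − 0.59²) = 14.37 and 85% power needs 298 students before clustering and dropout, and 728 after both. That is a separate matter and neither supports nor weakens this point.

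**2. What cancels.** Write a student's value at visit *t* as fixed part + class effect C + class-by-visit effect CT(t) + student effect S + residual e(t). The change is then

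D = fixed part + [CT(2) − CT(1)] + [e(2) − e(1)].

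C and S are gone. A model holding only C (with or without S) has no term for CT(2) − CT(1).

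**3. Size with a student effect in the model.**
- Variance of D per student: 2 × SD² × (1 − r)
- Class-level part of it: 2 × SD² × ICC × (1 − a)
- ICC of change: ICC × (1 − a)/(1 − r)
- Variance inflation left out: V = 1 + (m − 1) × ICC × (1 − a)/(1 − r)
- Actual error of a nominal 5% test: 2Φ(−1.96/√V)

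For example, at a = 0.8, V = 1 + 28 × 0.034 × 0.2/0.41 = 1.46.

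| a | V | Error, formula | Error, simulated |
|---|---|---|---|
| 1 | 1.00 | 5.0% | 4.8% |
| 0.9 | 1.23 | 7.7% | not run |
| 0.8 | 1.46 | 10.5% | 10.6% |
| 0.5 | 2.16 | 18.2% | 19.1% |
| 0 | 3.32 | 28.2% | 28.3% |

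The simulated column uses 20,000 null data sets of 6 classes of 29.

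If the ICC of 0.034 is applied to change itself, V = 1.952 and the error is 16.1%. This corresponds to a = 0.59, since (1 − a)/(1 − r) is then 1. Standard errors are too small by 1 − 1/√1.952 = 28%. With 20% dropout, m = 23.2 and the error is 13.9%. An ICC of change of 0.01 gives 8.3%, and 0.05 gives 20.6% (both at m = 29). Mixed models fitted to 300 simulated data sets, with class and student effects, rejected 15.3% of the time when change had an ICC of 0.034, and 3.7% when there was no class-by-visit variance.

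**4. Size with class as the only random effect.** Independent residuals treat a student's two values as unrelated. The assumed variance of D is then 2 × SD² × (1 − ICC), when the true student-level variance is 2 × SD² × (1 − r). The ratio of true to assumed variance is V × 0.41/0.966, which is 0.42 at a = 1 and 1.41 at a = 0. Simulated error rates were 0.2% (a = 1), 1.2% (0.8), 4.2% (0.5) and 9.9% (0). The two omissions pull in opposite directions.

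**5. After the fix.** A test of class-level change on 6 − 2 = 4 degrees of freedom, equivalent in balanced data to a class intercept on the change score, rejected 4.9% to 5.4% of the time over the same range of *a*.

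**The case against.** The strongest objection is that the article makes change from baseline the outcome at 24 weeks, and under that reading a class intercept carries the clustering and the test holds about 5%. This stands as far as it goes, so the 24-week analysis cannot be called invalid as written. It does not settle the matter: the same sentence keeps baseline as a level of time and keeps group-by-time, and the maintenance analysis does not mention change.

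The second objection is that the text says random effect, not random intercept, and an article may leave the covariance structure to a fuller document. A class-by-visit term is therefore not excluded. But the article itself chooses both the cluster term and the tested contrast, and in their ordinary meaning the two do not fit together.

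The third is that an inflated error rate requires an unnamed student effect to be present and an unnamed class-by-time effect to be absent. This also stands. Read literally, with class as the only random effect, the test is conservative over much of the range. The direction of error is not established.

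A reader might infer that the trial's false-positive rate is about 16%, or that its confidence intervals are too narrow throughout. The article does not support either. The 16% needs a student effect and the ICC for activity applied to change, and a class effect that is stable over time cancels legitimately. Nor are classes the randomised unit: schools are, so even a sound class-level test holds its error only if schools add no variance in change of their own.

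**Conclusion.** The point holds in conditional form. The 24-week specification contradicts itself. In any version that keeps baseline as a level of time, which is how the maintenance analysis is written, the named class effect does not deliver the clustering adjustment that the sample size assumes, unless class effects are constant between visits.

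The consequence depends on two things the article does not state: the stability of class effects and the student-level covariance. With a student effect, the nominal 5% lies between about 5% and 28%; even fairly stable classes (autocorrelation 0.8) roughly double it. Without one, it lies between about 0.2% and 10%. These figures rest on six classes of 29 with complete data. The number of classes is itself inferred: the abstract aims for about 140 students, and the article gives three classes per school in one section and two in another.

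This is more than missing detail, because the stated terms conflict. It is less than proof that the primary test is anti-conservative.

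**What to change.** State one model for each time point. Either of these works:

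- **Single value per student.** Analyse the 24-week value (or change), and separately the 48-week value, adjusted for baseline, with treatment as the fixed effect of interest and a class random intercept. Remove time and group-by-time from this description.
- **Repeated measures.** Keep baseline, 24 and 48 weeks with group-by-time, and include student and class-by-visit random effects.

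Use small-sample degrees of freedom (Satterthwaite or Kenward-Roger) in both. Because schools are randomised, any school-level adjustment should be a school intercept in the single-value form or school-by-visit in the repeated-measures form; a school intercept alone cancels from group-by-time.

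The change is to wording only and needs no new data. The cost is wider intervals and few degrees of freedom: 4 with six classes, and fewer at school level, since six classes would mean two or three schools. In simulation with an ICC of change of 0.034 and a true effect of 5 min per day, power was about 21% for a class-level test on 4 degrees of freedom, against an apparent 53% when students' changes were treated as independent. The lower figure is the price of a test that holds its error rate with so few classes.

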## Abstract

This trial aims to investigate the effects of the ActTeens physical activity program, on adolescents’ physical activity level, health-related fitness, cardiometabolic and mental health. The trial will aim to recruit ~140 adolescents (aged 13–14 years). Participants will be randomized into either intervention or control groups. The intervention will be guided by social cognitive theory and self-determination theory and implemented over one school term (24-weeks). The *ActTeens Program* will include: (1) structured physical activity sessions delivered within physical education, including movement-based games and dynamic stretching warm-ups; resistance training skill development; high-intensity training workouts; and cool-downs; (2) self-monitoring plus goal setting for physical activity by pedometer-smart wearable; and (3) healthy lifestyle guidance (social support) by WhatsApp® messages about healthy eating and regular physical activity for the intervention and parents groups. Study outcomes will be assessed at baseline, 24-weeks from baseline, and 12-months from baseline. Physical activity (accelerometer) is the primary outcome. Secondary outcomes include muscular and cardiorespiratory fitness, cardiometabolic profile, and mental health. A process evaluation will be conducted (i.e., recruitment, retention, attendance, and program satisfaction). This project will have the potential to address many questions and debates regarding the implementation of physical activity interventions in low-and- middle-income countries.

**Trial registration:** ClinicalTrials.gov NCT05070377. Registered on 7 October 2021.

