### Blinding and randomisation

Randomization will occur among schools that have been recruited and have completed baseline assessments. The schools will be matched based on the following characteristics: school area-level socioeconomic status (i.e., using Socio-Economic Class ABEP) [44]. Schools will be randomised to either a control or an intervention condition by an independent researcher using a computer-based random number generator. We will aim to recruit two classes per school (ie, one class of 8 grade and another of 9 grade) (Fig 1). Schools selected to the intervention condition will participate in the program during the study period, whereas schools allocated to the control condition will continue usual school practice.

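### Schools are randomised, but the model carries only a class random effect and adds school conditionally; if school-level variance remains, standard errors will be too small, and the few schools implied cannot check this

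*Protocol article*

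**What the plan says.** All references are to the protocol article.

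- **Allocation** (Blinding and randomisation): "Schools will be randomised to either a control or an intervention condition by an independent researcher". Beforehand, "The schools will be matched based on the following characteristics: school area-level socioeconomic status". The recruitment aim is given as "We will aim to recruit two classes per school".
- **Model** (Analysis plan): "Time and treatment will be included as fixed factors, with school class will be included as a random effect".
- **Reason for leaving school out** (Analysis plan): earlier studies are cited to the effect that "school-level clustering is negligible after accounting for clustering at the class level".
- **Condition for putting it back** (Analysis plan): "if requerid, we will test this assumption and additionally adjust our analyses for school-level clustering". No criterion is attached.
- **Sample size calculation**: 174 students, an average class of 29, three classes per school, an ICC of 0.034 applied at class level, and 20% dropout. There is no school-level term.
- **Abstract**: "Participants will be randomized into either intervention or control groups", which does not describe allocation by school.

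The number of schools is not stated.

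**The concern.** Treatment varies only between schools. Whatever makes classes in the same school change alike is therefore part of the noise in the treatment contrast. A model with class as its only cluster treats classes that share a school as independent replicates. It takes both its error term and its degrees of freedom from them.

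If school variance in the change is above zero, confidence intervals are too narrow and false-positive claims too frequent. The same model is specified for the primary and the secondary outcomes, so the choice reaches all of them, although the size of any effect may differ by outcome.

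The conditional clause does not protect against this unless the trial's own data can show whether school matters. With very few schools they cannot.

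**Working it through.** **1. What the plan itself computes.** The only clustering figure is the class-level correction: 1 + (29 − 1) × 0.034 = 1.952. Nothing corresponds to school.

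**2. How many schools.**
- Two classes per school (Blinding and randomisation): 174 / (2 × 29) = 3.
- Three classes per school (Sample size calculation): 174 / (3 × 29) = 2.
- Forming matched pairs needs an even number, so three would become four.

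**3. Standard error.** Let ρs and ρc be the school and class ICCs, c the classes per school and m the pupils per class. For a balanced design,

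true SE / class-only SE = √{[ρs + ρc/c + (1 − ρs − ρc)/(cm)] / [(ρs + ρc)/c + (1 − ρs − ρc)/(cm)]}.

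Hold the total at 0.034 with m = 29. The split between levels is assumed, because the article gives none.

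| Share of 0.034 at school level | c = 2 | c = 3 |
|---|---|---|
| 0% | 1.00 | 1.00 |
| 25% | 1.06 | 1.12 |
| 50% | 1.12 | 1.23 |
| 100% | 1.23 | 1.42 |

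Example, 100% and c = 2: √[(0.034 + 0.966/58) / (0.017 + 0.966/58)] = √(0.05066/0.03366) = 1.23.

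**4. Type I error of a nominal 5% class-level test.** Pupils analysed per class: 29 × 0.8 ≈ 23. The variance of a class mean within a school is v = ρc + (1 − ρs − ρc)/23.

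With one school of three classes per arm, the class-level test has 4 df and critical t 2.776. It estimates v/3 per arm where the truth is ρs + v/3. Its error rate is P(|t₄| > 2.776/k), with k = √[(ρs + v/3)/(v/3)].

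- ρs = 0.01, ρc = 0.034: v = 0.0756, k = √(0.0352/0.0252) = 1.18, P(|t₄| > 2.35) = 0.08.
- ρs = 0.02, ρc = 0.034: v = 0.0751, k = √(0.0450/0.0250) = 1.34, P(|t₄| > 2.07) = 0.11.
- ρs = 0.034, ρc = 0: v = 0.0420, k = √(0.0480/0.0140) = 1.85, P(|t₄| > 1.50) = 0.21.

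A simulation that falls back on the pooled error when class variance is estimated at zero gives nearly the same values, and adds the layout with two schools per arm:

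| Assumed school ICC | 1 school × 3 classes per arm | 2 schools × 2 classes per arm |
|---|---|---|
| 0 | 5% | 5% |
| 0.01, added to class 0.034 | 8% | 6% |
| 0.02, added to class 0.034 | 11% | 8% |
| 0.034, class 0 | 20% | 11% |

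**5. Can the trial check the assumption?**
- Two schools: 2 − 2 = 0 df for school variance. No check is possible.
- Four schools of two classes: an F test on 2 and 4 df has critical value 6.94. At ρs = 0.02 and ρc = 0.034 the ratio is inflated by 1 + 2 × 0.02/0.0751 = 1.53. Power is P(F₂,₄ > 6.94/1.53 = 4.53) = 0.094.
- With the total held at 0.034 and classes of 29, power is 7% (25% share at school level), 9–11% (50%) and 16–22% (100%) for three or four schools.

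**6. Degrees of freedom for the treatment effect, without a pair term.**

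| Schools | School-level df, critical t | Class-level df, critical t |
|---|---|---|
| 3 | 1, 12.7 | 4, 2.78 |
| 4 | 2, 4.30 | 6, 2.45 |

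**The case against.** **Negligible may be true.** The plan cites earlier work that little school clustering is left once class is modelled, and that source cannot be examined here. At zero school variance the class-only test holds its 5% level. This stands. A reader might infer that the standard errors will certainly be too small; the documents do not support that.

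**Change scores and matching reduce the problem.** The outcome is analysed as change from baseline with a group-by-time term, and schools are matched on area socioeconomic status. Stable differences in facilities or area largely cancel in the change. A reader might infer that all such effects land on the treatment contrast; that overstates it. What matters is variation between schools in the change. The calculations compare one set of class means and model neither feature, so their percentages illustrate and do not estimate this trial's error rate.

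**The variances are assumed.** Adding 0.01–0.02 to a class ICC of 0.034 exceeds the total clustering in the article, and putting all of it at school level reverses what the plan believes. The 0.034 is given for physical activity only. All of this stands, and is why a range that starts at zero is shown.

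**No test-and-drop rule is written.** A reader might infer that school is to be dropped after a non-significant test. The text names no significance test and no threshold, and its condition governs both the checking and the adjusting. The F-test figure shows what such a check could achieve, not what the protocol prescribes. Details of a test may well sit in a fuller plan. The default model, however, is stated, and it leaves out the randomised unit.

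**Conclusion.** The concern holds in conditional form. The stated model omits the unit that was randomised and brings it back only under an undefined condition. If school-level variance in the change exists, the class-only standard error is too small: the true value is 1.06–1.23 times as large with two classes per school, or 1.12–1.42 times with three, when 25–100% of an ICC of 0.034 lies at school level. The illustrative type I error runs from 5% with no school variance, through 6–11% at an added school ICC of 0.01–0.02, to 11–20% if all of the 0.034 is at school level.

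These sizes rest on an assumed split of the ICC, balanced classes, and layouts of two or four schools. The school count is inferred from the article's arithmetic, which yields two or three; four follows only if pairs are completed. The conclusion does not depend on the exact count. The check is impossible with two schools and weak with three or four, so finding no evidence of school clustering could not justify leaving school out.

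**What to change.** In the protocol article:

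1. State the number of schools per arm and the classes in each.
2. In the Analysis plan, replace the conditional clause. School is always a random effect, with class nested in school. The treatment effect is tested with Satterthwaite or Kenward-Roger degrees of freedom at school level.
3. State how the matching on socioeconomic status enters the model. With four schools in two pairs, a pair term leaves 2 − 1 = 1 df.
4. If there is only one school per arm, report the between-arm difference descriptively, with no confirmatory p-value.
5. Describe the design as school cluster-randomised in the Abstract, in line with Blinding and randomisation.

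The edits are to wording and analysis, but the statistical cost is large. Before any change in the standard error, the critical value alone widens the interval by 4.30/2.45 = 1.8 times with four schools and 12.7/2.78 = 4.6 times with three, and a pair term widens it further. The stated precision and power should be restated on that basis. More schools, rather than more pupils per school, is what would recover them.
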